### Design and setting

The project will be based on different data sources: subproject 1a) registry data on team and organizational structures from the German Guide for hospice and palliative care services as well as model contracts in all German regions and 1b) clinical routine patient data from electronic medical record (EMR) of a sample of SAPV teams, subproject 2) patient-reported outcomes in a sample of about 50 SAPV teams, each collecting data from 25 patients, subproject 3) qualitative interviews with members of SAPV teams and linked providers involved in SAPV, like nursing and hospice services, subproject 4) survey data from GPs and subproject 5) health insurance fund claims data from patients who have died in 2016 and were covered by the health insurance fund BARMER.

This study is conducted in Germany from July 2017 to June 2019 and includes a transdisciplinary and multi-method design. The overall project is characterized by a cross-project use of data and a combination of quantitative and qualitative research designs. The focus of the quantitative research is obtaining a representative cross-section of the German SAPV, for instance by mapping the 17 Regional Associations of Statutory Health Insurance Physicians (KV). These regions are equivalent to the 16 Federal German States, but North Rhine-Westphalia is divided into North Rhine and Westphalia-Lippe.

From a sample of about four SAPV teams per KV, aggregated data of approximately 70 patients per SAPV team are associated to structural characteristics of the selected teams (subproject 1). Following this, a patient survey of a sub-group of about 25 patients per SAPV team will be conducted, focusing on the quality of care from the perspective of patients and on linking these findings to individual demographic and clinical data (subproject 2). A postal survey of about 1200 GPs using a standardized, quantitative study design in eight KV domains is conducted to explore their involvement in and needs regarding SAPV (subproject 4). An analysis of palliative care based on claims data [17, 28], provided by the health insurance fund BARMER, is performed to represent the utilization of the different types of in- and outpatient palliative care services in Germany (subproject 5). Data which cannot be obtained via quantitative research designs – such as interpretations and evaluation categories of quality of care by SAPV teams and their network of care givers and service providers – will be explored by a qualitative design. This is carried out as an on-site field study involving comparative case studies. Ten SAPV teams, each of which represents a minimal or maximal type within a set of contrasting structural characteristics, will be explored by means of field trips of several days duration (subproject 3). Wherever possible, synergies between the SAVOIR subprojects will be used. This involves the exchange of data (e.g. regarding the empirically grounded selection criteria for SAPV teams) and cooperation regarding content and concept of the subprojects.

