In 2016 about 55.000 patients (6% of the deceased in Germany) had received SAPV [11] before their death. This proportion is well below the estimated 10% of dying patients with a need for specialist palliative care at home [2]. However, recent analyses in Germany focused mainly on the description of (regional) SAPV-structures and utilization [12–16] as, for instance, the study “Faktencheck Gesundheit” investigated regional disparities of SAPV prescriptions [17]. Until now, no nationwide assessment of SAPV from different perspectives has been conducted [18]. In our view, there is a special need for an evaluation of the SAPV directive taking into account:The heterogeneity of organizational structures and processes and their effects on patient care: Heterogeneity is particularly represented by different forms of ownership, team structure, integration of different professions, reimbursement systems and regional factors like urban or rural settings [14]. This also leads to different levels of involvement of the SAPV teams (consultation, coordination of care, partial or full provision of care). The potential consequences of these different contractual elements on patients´ care are mostly unknown.As palliative care is a multi-professional, patient-centered care model, different perspectives of affected persons and involved professionals should be considered [19].Although the individual needs of patients and their relatives are key aspects of the SAPV directive, there are no formal requirements for a corresponding quality assurance. Available research does not focus on the patient perspective at all [17] or only does so in specific scenarios [14, 20]. Assessing quality of care without consideration of the patients perspective will remain incomplete [21]. With the help of the questionnaire QUAPS (Quality Assurance in Outpatient Palliative Care) we will be able to investigate quality of SAPV from patients’ perspective [22].Since SAPV is acting in a complex social environment of patients, relatives and health care professionals, the evaluation of overall quality of palliative care requires an adapted and differentiated analysis considering cooperation and perspective of these stakeholders. Accordingly, SAPV is a process of interactions of these participants, located in the individual patient’s environment. Therefore it is necessary to describe the local cooperation of health care professionals.General practitioners (GP) are substantially involved in the end of life care of their patients [23]. They play an important role in AAPV, can introduce SAPV to patients’ care by medical prescription and often remain subsequently involved [24]. This key role strengthens the need of assessing the impact of GPs on the quality of SAPV in connection to patients, other health professionals and the SAPV directive.The interface between general and specialist outpatient palliative care appears to be under-explored [11, 25]. Furthermore, available claims data studies focused on a small selection of specific aspects of palliative care [26]. Investigation of utilization and costs of different types of palliative care using claims data is a useful addition. On that basis it might be possible to find hints for over-, under- and missupply of end-of-life-care considering health economic perspectives.Against the background of the requirements of the national ethics council [27], it is an important goal to highlight the patients’ welfare as the leading principle in medical care. Taking this into account, it is necessary to focus on potential shortage of outpatient palliative care in specific patient groups, for example patients with non-malignant disorders.

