##### Data analyses

We will conduct a descriptive analysis of quantitative variables and will also perform univariate and multivariate regression analyses on the association between independent and dependent variables.

#### Subproject 5

SAPV in comparison to other types of palliative care: patient characteristics and resource utilization (payer’s perspective).

*Hypotheses:* The type, extent and quality of palliative care a patient receives during the last months before death differs according to patient characteristics as well as regional structures of palliative care provision.

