##### Study population

About 95,000 adults throughout Germany, insured, with the health insurance fund BARMER and time of death in the year 2016.

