##### Data collection

Pseudonymous individual claims data (according to §§ 284, 295, 300, 301, 302 of the Fifth Book of the Social Code, SGB V) are made available via the Scientific Data Warehouse of the health insurance fund BARMER. Additional variables and value lists, which are considered relevant for the planned investigation (i.e. specific billing codes for AAPV and SAPV as well as hospices care data), were supplemented. Relevant periods of observation of received health insurance fund services include the last six and three months before death, the time period between months 12 and seven before death is defined as pre-observation period. The assignment of patients to cohorts and subgroups is executed by means of defined outpatient billing codes or hospital-based operation and procedure codes (OPS). We use preexisting indicators and – under consideration of the limitations of claims data - develop and quantify new and eligible indicators to describe distinct types of palliative care, their utilization and their quality of care. The study population will be characterized by socio-economic, administrative diagnoses and other care-specific attributes. In addition, we will calculate measures aimed at describing the quality of palliative care based on variables available in claims data.

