##### Data analyses

Outcome measures and patient characteristics will be described statistically for each cohort and region. For the comparison of outcome measures between cohorts and regions we intend to use multivariate regression analyses.

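### Subproject 5 is worded as representing palliative care use in Germany, but its data are one fund's decedents, levels are only described, and the single-insurer source is not listed as a limitation

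*Protocol article*

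**What the plan says.** The Design and setting section gives the purpose of the claims analysis in subproject 5: it "is performed to represent the utilization of the different types of in- and outpatient palliative care services in Germany". The same section sets the tone for all quantitative parts: "The focus of the quantitative research is obtaining a representative cross-section of the German SAPV".

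The population under Subproject 5, Study population, is "About 95,000 adults throughout Germany, insured, with the health insurance fund BARMER and time of death in the year 2016". The analysis is given in two sentences. For levels: "Outcome measures and patient characteristics will be described statistically for each cohort and region". For contrasts: "For the comparison of outcome measures between cohorts and regions we intend to use multivariate regression analyses". The data collection text adds that "The study population will be characterized by socio-economic, administrative diagnoses and other care-specific attributes", without saying which of these attributes enter a model.

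The subproject's own hypothesis is that the type, extent and quality of care "differs according to patient characteristics as well as regional structures of palliative care provision".

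The Discussion lists three limitations for subproject 5: incomplete SAPV claims, too little detail on provider qualification, and no clinical or patient-reported data. It does not say that the decedents all belonged to one insurer.

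**The concern.** The stated target is use of services in Germany; the observed population is the deceased members of one fund. The article states no step that leads from one to the other. By the subproject's own hypothesis, care depends on who the patients are and on where they live. A crude share therefore depends on the fund's membership mix, and it describes Germany only as far as that mix resembles the mix of all decedents.

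With some 95,000 records the confidence intervals will be very narrow and will show none of this. Levels matter to the project. The Background argues from the share of decedents reached by SAPV and asks about over-, under- and missupply, and the results are to feed recommendations on the SAPV directive.

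The Background also says that the directive leaves room for individual agreements between funds and providers, with over 290 contracts nationwide. One fund's use could thus differ from that of other funds even among patients of the same age, sex and region.

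**Working it through.** The plan states no figure for the national coverage of the data, so there is none to reproduce. The check has three steps.

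**1. How much of the target is observed**

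Inputs: "In 2016 about 55.000 patients (6% of the deceased in Germany) had received SAPV" (Background), and about 95,000 decedents (Subproject 5, Study population).

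- Implied deaths in 2016 = 55,000 / 0.06 = about 917,000. Allowing for rounding of both inputs: 54,500 / 0.065 = about 838,000 to 55,500 / 0.055 = about 1,009,000.
- Share observed = 95,000 / 917,000 = 10.4%, range 9.4% to 11.3%. This is approximate, because the numerator is restricted to adults.

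About nine tenths of deaths are therefore outside the data.

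**2. Sampling error of a crude share**

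Take 6% as an example share.

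- All decedents: SE = sqrt(0.06 × 0.94 / 95,000) = 0.077 points; 95% half-width = 1.96 × 0.077 = 0.15 points.
- Average KV region, assuming 17 equal regions: 95,000 / 17 = 5,588; SE = sqrt(0.06 × 0.94 / 5,588) = 0.318 points; half-width = 0.62 points.

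**3. What a difference in mix would do**

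Let stratum k have rate r_k, share v_k among the fund's decedents and share w_k among all decedents. Then

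crude − standardised = Σ (v_k − w_k) × r_k,

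which for two strata is (v_1 − w_1) × (r_1 − r_2). The documents give neither v, w nor r, so the following values are assumptions:

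| Difference in stratum share | Difference in rate between strata | Shift of crude share | Relative to national half-width |
|---|---|---|---|
| 5 points | 1 point | 0.05 points | 0.3 |
| 5 points | 4 points | 0.20 points | 1.3 |
| 10 points | 2 points | 0.20 points | 1.3 |
| 15 points | 4 points | 0.60 points | 4.0 |

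If the same shifts applied within an average region, they would be 0.05 / 0.62 = 0.1 to 0.60 / 0.62 = 1.0 times the half-width there. The shift does not depend on N. It can be smaller or larger than the sampling error, and its true size and direction cannot be derived from the documents.

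**The case against.** The strongest reply is that this is a condensed article: reference populations and weights are normally left to the full protocol or analysis plan, which are not shown. Further, the Aim of the study describes subproject 5 as describing types of care by means of fund claims data, several sections restrict the population to this fund, and the verb in the purpose statement can be read as depicting rather than estimating. No passage plans to scale results to Germany.

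Part of this stands. The absence of standardisation is only an absence from the article, and it would not be a finding by itself. What remains is in the article's own text: a purpose worded for Germany, and a list of limitations that omits the single insurer although those for subprojects 2, 3 and 4 do say who may be over-represented.

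Three stronger readings are tempting and not supported:

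- A reader might infer that membership mix outweighs all other error. No profile of the fund's decedents is given, the shift in an average region is at most about one half-width under the assumptions above, and the Discussion admits incomplete SAPV claims, which act directly on the SAPV share.
- A reader might infer that regional and cohort comparisons are biased in the same way. Multivariate regression is planned for these and patient attributes are available, so mix may already be adjusted for, although the covariates are not named. Reporting by region also takes regional mix out of each regional figure.
- A reader might want to validate the fund's SAPV share against the national 6%. The two are not comparable: subproject 5 covers adults, a window of six months before death and incomplete claims, and the national figure states no window or age limit. A gap could arise from any of these.

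**Conclusion.** The point holds for crude utilisation levels and for the wording. A statement about Germany is attached to data on about 10% of deaths, all from one insurer, with only description stated for levels and no limitation naming the source. The size of the error is unknown. The range of 0.05 to 0.60 points rests wholly on assumed differences in mix and rates, and shows only that a narrow interval from 95,000 records does not bound it. That the fund's mix differs at all is plausible but not shown. The point does not carry over in the same strength to the regression comparisons, and no particular recommendation on the directive can be shown to change.

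**What to change.** 1. Report the main utilisation shares of subproject 5 both crude and directly standardised to all adult deaths in Germany in 2016. Standardise by age group and sex, and for national figures also by KV or federal state. Where the reference table is by federal state, the two KV regions of North Rhine-Westphalia can be combined.
2. Reword the purpose in Design and setting so that unstandardised figures are stated for this fund's decedents only.
3. Add the single-insurer source to the limitations of subproject 5. Say that standardisation leaves differences due to fund-specific contracts, morbidity and socio-economic mix uncorrected, so that standardised figures are not taken as fully national.

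The cost is one reference table from national death statistics, a weighting step and slightly wider intervals in small cells. No further patient data are needed.

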### Data management

The data management and all required steps of data preparation (for example check for plausibility and integrity) will be located at the Center for Clinical Trials at University Hospital Jena. All participant data will be pseudonymized. In addition, data collected from the subprojects will be managed at the corresponding institution: in subproject 4, data from the survey will be anonymously evaluated. The claims data analysis in subproject 5 will be based on the recommendations of the “Good Practice Secondary Data Analysis” [29]. The data management of subproject 3 will be located at the Center for Interdisciplinary Health Research (ZIG) at the University of Augsburg.

### Ethics

Votes from the local ethics committees of the respective institutions were obtained from Jena University Hospital (No. 5312–10/17, 5316–10/17, 5317–10/17), University Medical Center Göttingen (No. 31/8/17) and University of Augsburg (06.09.2018).

### Sample and procedure

#### Subproject 1

Structural characteristics of SAPV and their impact on quality of care.

##### Hypotheses

Differences in provision of care are associated with different team structures and regulatory foundations.

##### Method and Design

The study encompasses three steps. Step 1a: Assesses SAPV structures nationwide (in cooperation with the DGP). Step 1b: Assesses regulatory structures, specifically the contracts between health insurance funds and SAPV teams (in cooperation with the BAG-SAPV). Step 2: SAPV teams provide patient data prospectively for 6 months. The patient data will be analyzed regarding regional and structural differences.

##### Study population

Step 1a/1b: Comprehensive assessment of SAPV teams and contracts. Step 2: Recruitment of 4 teams per region (*n* = 17). Assessment of 70 patients per team in six months, resulting in 5.950 patient data sets.

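### Subproject 1's stated total of 5,950 patient data sets does not follow from its own design: 4 teams × 17 regions × 70 patients gives 4,760, so the printed figure is 25% too high

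*Protocol article*

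**What the plan says.** Under Subproject 1, Study population, step 2 is sized in two sentences. The first sets the number of teams: "Recruitment of 4 teams per region", with 17 given as the number of regions. The second gives the yield: "Assessment of 70 patients per team in six months, resulting in 5.950 patient data sets". The point in 5.950 is the German thousands separator, so the total is 5,950.

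The Design and setting section describes the same sample with the same inputs, slightly softened: "From a sample of about four SAPV teams per KV, aggregated data of approximately 70 patients per SAPV team". It also confirms the region count, in describing a representative cross-section obtained by "mapping the 17 Regional Associations of Statutory Health Insurance Physicians (KV".

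Under Data collection, the article adds that teams ask every patient admitted during the six months for permission to extract data. It gives no expected refusal rate, loss allowance or over-recruitment factor for Subproject 1. Under Data analyses, the step 2 data go into hierarchical multilevel models that relate structural predictors to patient and care parameters.

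**The concern.** The total is presented as the product of the inputs beside it, and it is not that product. Either the total is wrong or one of the inputs is.

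This matters beyond tidiness because of what Subproject 1 is for. Its hypothesis links differences in care to team structures and regulation. A structural characteristic of a team takes one value per team, so the number of teams largely determines how precisely its effect can be estimated. Adding patients within teams helps much less. The article never prints a total number of teams for this subproject. A reader who multiplies the inputs gets 68. A reader who divides the stated total by 70 gets 85. These are different cluster-level sample sizes for the same models.

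The benchmark for recruitment is also unclear. If the study collected 4,760 data sets, it would have met its target in full on one reading and reached 80% of it on the other (4,760 / 5,950 = 0.80).

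**Working it through.** **Inputs**

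- Teams per region: 4 (Subproject 1, Study population; about four in Design and setting).
- Regions: 17 (both sections).
- Patients per team in six months: 70 (Subproject 1, Study population; approximately 70 in Design and setting).
- Stated total: 5,950 (Subproject 1, Study population).

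**Attempt to reproduce the stated total**

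- Teams: 4 × 17 = 68.
- Data sets: 68 × 70 = 4,760.
- Gap: 5,950 − 4,760 = 1,190.
- Relative gap: 5,950 / 4,760 = 1.25, so the printed figure is 25% above the product.

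The stated inputs do not reproduce the total.

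**What would give 5,950**

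| Reading | Calculation | Result | Supported by the text? |
|---|---|---|---|
| 4 teams, 17 regions, 70 patients | 4 × 17 × 70 | 4,760 | Yes, in two sections |
| 4 teams, 16 regions, 70 patients | 4 × 16 × 70 | 4,480 | No, and the gap widens |
| 5 teams, 16 regions, 70 patients | 5 × 16 × 70 | 5,600 | No |
| 5 teams, 17 regions, 70 patients | 5 × 17 × 70 | 5,950 | No, 5 appears nowhere |
| 4 teams, 17 regions, more patients per team | 5,950 / 68 | 87.5 per team | No, 70 is stated twice |
| 4,760 inflated for 20% loss | 4,760 / (1 − 0.20) | 5,950 | No, no allowance is stated |

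The gap of 1,190 is exactly one further team per region: 1 × 17 × 70 = 1,190. This suggests, as inference only, that the total was calculated with five teams per region.

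**Comparison with the other sample totals in the article**

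- Subproject 2: 50 teams × 25 patients = 1,250, as printed.
- Subproject 4: 8 regions × 750 GPs = 6,000, and 6,000 × 0.20 = 1,200, both as printed.

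These totals are plain products of their inputs, and they work. The Subproject 1 total is written in the same way and does not.

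**Consequence for team-level effects**

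Let J be the number of teams and m the number of patients per team. With equal team sizes, the variance of an estimated team-level effect is proportional to (between-team variance + within-team variance / m) / J. If m stays at 70 and the variances and the spread of the predictor are unchanged, the numerator cancels. Then

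SE(68 teams) / SE(85 teams) = √(85 / 68) = √1.25 = 1.118.

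Standard errors are therefore about 12% larger with 68 teams than a reader who assumed 85 would expect. With m fixed, this ratio does not depend on the intraclass correlation.

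**The case against.** The best argument on the other side concerns direction and weight, since the arithmetic is not in dispute.

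First, the article does not show which element is wrong. Five teams per region gives 5,950, but so does a 20% loss allowance on 4,760, and so would 87.5 patients per team. Because data extraction needs patient permission, a loss allowance is conceivable. This stands in part: the 85-team reading is an inference. The allowance fits the wording poorly, however, because the article says "resulting in 5.950 patient data sets", which describes data sets obtained and not patients approached. The inputs also appear in two sections and the total in only one, so the balance favours 4 and 70.

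Second, Design and setting hedges both inputs with words for approximation. That is true of that section, but the Study population section gives 4 and 70 without qualification. A 25% excess is more than such hedging can absorb.

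Third, little depends on the number. No power calculation, stopping rule or test uses 5,950, and the achieved count will follow admissions and consent. The team count can be derived from the sentence just before the total. This stands, and it limits the harm: no claim about power or type I error is invalidated. The 12% figure is also conditional. It assumes 85 teams as the alternative, equal team sizes and unchanged variances. It applies to predictors that vary between teams. Predictors set by regional contracts depend more on the 17 regions, and that number is the same on either reading.

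None of these points makes the printed total agree with the printed design.

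**Conclusion.** The concern holds. On the article's own inputs, step 2 of Subproject 1 yields 68 teams and 4,760 data sets. The stated 5,950 exceeds this by 1,190, or 25%, and nothing in the text accounts for the difference. This conclusion rests only on multiplying three stated numbers.

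Two further statements are conditional. That the total came from five teams per region is inferred from an exact numerical match. The roughly 12% difference in standard errors holds for team-level predictors, comparing 68 with 85 teams at 70 patients each, with equal team sizes and unchanged variances. The practical effect is a misstated sample size for the structural analysis and an unclear recruitment target, without any loss of a planned power or error rate.

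**What to change.** Restate the step 2 target as 68 teams (4 × 17) and 4,760 patient data sets (68 × 70) in the Subproject 1 Study population section.

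If five teams per region were intended, keep 5,950, change the team count to five in both the Study population and the Design and setting sections, and give the total as 85 teams. If the total was meant to include an allowance for refusal or loss, state its size and say that 5,950 is the number of patients approached, with 4,760 data sets expected.

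In each case, print the total number of teams next to the total number of patients, since the team count drives the precision of the structural effects.

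If the four-team design stands, the cost is one corrected number and a less favourable printed sample size, with no extra patients or teams. If five teams were meant, the correction is still textual, but the recruitment task is 17 teams larger (85 − 68) than the text now states.
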